#### Follow-Up 6-Monthly Visits

Follow-up visits will be made every 6 months at the 6th, 12th, 18th month of the study period to the homes of both the groups. The parents in intervention group will receive DHVs and ELs by the dental home visitors, while those in the control group will receive only ELs to be delivered by the dental home visitors. The researchers will check the dental visit diary from both groups at each 6-month visit.

#### The 2-Year Follow-Up Data

At the end of the 2-year study period, the researchers will visit the subjects’ homes from both the intervention and control groups and repeat the same dental examination, complete the ECOHIS questionnaire, and gather the information from the dental visit diary. At the 2-year follow-up visit, the subjects will be 7 or 8 years old. It is anticipated that, should new caries develop, the majority will be on primary posterior teeth and first permanent molars. Adhering to the NOHPS protocol, the follow-up oral examination will be carried out to collect the number of new decayed, missing (due to caries) and filled posterior deciduous teeth (dmft), and the number of decayed, missing (due to caries) and filled first permanent molars (DMFT). The children will be examined while sitting on a portable dental chair at their homes. The visual oral examination will use disposable mouth mirrors with natural daylight for illumination, supported by a Daray lamp where necessary. No radiographs will be taken, and no treatment will be provided. Children who have been assessed with obvious caries will be advised to visit a dental clinic for further assessment and treatment if necessary. The researcher will offer to provide information or make the necessary arrangements for families who wish to have further assessment at a dental clinic.

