### Study Measures

#### Outcome Measures

The primary outcome of this study is the incidence of new caries, measured by the number of children included in the study with new caries, over a period of 2 years. The difference in the number of children with new caries between the intervention and the control groups will be considered as the number of children prevented from developing caries.

The calculated cost of the DHVs used in the intervention will include staff salaries, telephone calls to make appointments, travelling allowances, and administrative costs. The ELs cost is estimated by using the market price to purchase leaflets, staff salaries, telephone calls, travelling allowances, and administration costs. The cost of preventing a child from developing caries will be calculated as the DHVs and ELs cost divided by the number of children prevented from new caries.

The secondary outcome of this study will be the improvement in OHRQoL over a period of 2 years. This is measured by the improvement in the early childhood oral health impact scale (ECOHIS) scores. The difference in the ECOHIS scores between the intervention and the control groups will be considered as the improvement in OHRQoL. The cost of improving the OHRQoL is calculated as the DHVs and ELs cost divided by the improvement in the ECOHIS scores.

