#### Number of New Carious Teeth

An oral examination will be conducted at baseline (before the start of the intervention) and at the end of the 2-year study period by researchers using the NOHPS protocol, which was based on the World Health Organization (WHO) recommendation published in 2013 [19]. The number of new decayed, missing (due to caries), and filled posterior deciduous teeth (dmft), as well as the number of decayed, missing (due to caries), and filled first permanent molars (DMFT) will be recorded. The dmft and DMFT caries assessment is chosen to ensure consistency with the assessment used by the OHD Ministry of Health Malaysia.

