#### Baseline Data

The baseline clinical data for all study participants will be based on the oral examination to be carried out at the kindergarten for all children with the parents’ consent. This examination will be conducted by researchers who have successfully attended the standardization training session. Oral examination will use a disposable mouth mirror. Caries assessment will be based on visual inspection, without invasive probing, and is diagnosed at the cavitation stage. Both primary and permanent teeth will be examined and if a permanent and a primary tooth occupy the same space, then only the status of the permanent tooth will be recorded. Caries assessment will adhere closely to the NOHPS criteria [17], which has been modified in 2013 from the WHO recommendations [21]. It is important to note that the WHO uses alphabets to denote caries status for primary teeth, however, NOHPS protocol uses numeral for both primary and permanent teeth. Hence, in this study, the following coding will be used: Sound teeth=0 (instead of A), Caries=1 (instead of B), Filled with caries=2 (instead of C) and Filled no caries=3 (instead of D). The teeth examination will begin from upper right to upper left and lower left to lower right quadrant and a tooth will be considered present when any part of it is visible [19,23]. No radiographs will be taken, and no treatment will be provided. Children who have been assessed with obvious caries will be advised to visit a dental clinic for further assessment and for treatment if necessary.

Baseline DHVs will be carried out and the parents in both the intervention and control groups will receive the ECOHIS questionnaire and a dental visit diary. The baseline ECOHIS questionnaire will be filled by the parents during the visit and returned to the researchers. The dental visit diary will be maintained by the parents and the research team will check the diary every 6 months. Parents will be informed to complete the diary every time their children visit the dental clinic.

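### The plan does not keep the 24-month caries examiner apart from the 6-monthly home visits or from the parent, so the primary outcome can be read with knowledge of the arm

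*Protocol article*

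**What the plan says.** The primary outcome is a yes/no result per child: "The primary outcome of this study is the incidence of new caries, measured by the number of children included in the study with new caries" (section Outcome Measures).

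The protocol article assigns the relevant tasks as follows.

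- **Oral examinations.** Number of New Carious Teeth places them at baseline and "at the end of the 2-year study period by researchers using the NOHPS protocol". The Standardization section identifies the examiners as researchers calibrated against a benchmark examiner.
- **Six-monthly home visits.** Follow-Up 6-Monthly Visits states what differs between the arms: "The parents in intervention group will receive DHVs and ELs by the dental home visitors, while those in the control group will receive only ELs". The same section adds: "The researchers will check the dental visit diary from both groups at each 6-month visit".
- **24-month visit.** The 2-Year Follow-Up Data sends the researchers to families' "homes from both the intervention and control groups and repeat the same dental examination". On the same occasion they also "complete the ECOHIS questionnaire, and gather the information from the dental visit diary".
- **Method of assessment.** Baseline Data: "Caries assessment will be based on visual inspection, without invasive probing, and is diagnosed at the cavitation stage". No radiographs are taken at either examination. At two years the examination is made in the home by daylight, with a lamp where needed.

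Allocation is by kindergarten, 1:1 (Sample Size and Randomization).

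**The concern.** One undivided role, the researchers, covers the diary checks at visits where the arms receive different things, and also the examination that yields the primary outcome. The final examination shares a home visit with the ECOHIS and the diary. Followed as written, the plan lets an examiner arrive already knowing the family's arm, or hear it from a parent who has had two years of counselling. Kindergarten allocation widens the exposure, since learning the arm of one family settles it for every other family from that kindergarten.

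The outcome is a visual call, and one borderline tooth can change a child's status. Outcome Measures takes the between-arm difference in affected children as the number prevented, and divides the intervention cost by it. Any shift in borderline calls would therefore enter both the effect estimate and the cost per child prevented.

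**Working it through.** **1. The roles side by side**

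| Task | When | Who, as written | Can the arm become known? |
|---|---|---|---|
| Delivery of home visits and leaflets | 6-month intervals | Dental home visitors | Yes, they deliver it |
| Diary check | 6, 12, 18 months, in the home | Researchers | Yes, the arms receive different things at these visits |
| Caries examination | 24 months, in the home | Researchers | Yes, from an earlier visit or from the parent |
| ECOHIS and diary collection | Same 24-month visit | Researchers | Yes, from the parent |

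No section divides the three researcher tasks among different people, fixes their order, or mentions masking. The only examiner safeguard is calibration, which aims at consistency within and between examiners. A perfectly calibrated examiner can still know the arm.

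**2. The plan's own sample size, for reference**

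Inputs from Sample Size and Randomization: incidence 5% versus 20%, 80% power, and a significance level written as 95%, read here as two-sided 0.05.

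- Uncorrected: n = [1.960·√(2·0.125·0.875) + 0.842·√(0.05·0.95 + 0.20·0.80)]² / 0.15² = 75.1 per arm.
- With continuity correction: (75.1/4)·[1 + √(1 + 4/(75.1·0.15))]² = 87.9, so 88 per arm and 176 in total.

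This matches the stated 176. The present point does not affect that figure.

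**3. Illustration of scale**

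Children per arm: 600 approached × 0.7 response × 0.7 retention = 294, so 147 per arm.

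Assumptions that are not in the document: no true effect; 20% true incidence in both arms (the plan's control figure); children independent; an aware examiner misses a fraction m of affected children in the intervention arm only.

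Observed proportions are p = 0.20 and q = 0.20·(1 − m), with d = p − q. SE₀ = √(2·p̄·(1 − p̄)/147) with p̄ = (p + q)/2. SE₁ = √([p(1 − p) + q(1 − q)]/147). Two-sided rejection = Φ[(d − 1.96·SE₀)/SE₁] + Φ[(−d − 1.96·SE₀)/SE₁].

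| m | q | d | SE₀ | SE₁ | Rejection | Children falsely counted as prevented (147·d) |
|---|---|---|---|---|---|---|
| 0 | 0.20 | 0 | 0.0467 | 0.0467 | 5.0% | 0 |
| 0.10 | 0.18 | 0.02 | 0.0458 | 0.0457 | 7.2% | 2.9 |
| 0.20 | 0.16 | 0.04 | 0.0448 | 0.0448 | 14.5% | 5.9 |
| 0.30 | 0.14 | 0.06 | 0.0438 | 0.0437 | 27.7% | 8.8 |

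A larger sample does not remove the distortion. At m = 0.30 the rejection rate is about 18% with 88 per arm and about 28% with 150 per arm.

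**The case against.** The strongest reply is that researchers is a team label. Baseline Data gives the diary check to the research team at large, whereas examiners are a narrower group who have passed the standardization training. A reader might infer that the same individuals check a family's diary and later examine the child. The documents do not say so, and different people could do each task. A reader might also infer that examiners deliver the intervention, but delivery belongs to the dental home visitors, who are named separately. Nor does the text say that researchers sit in on the counselling.

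A second tempting inference is that the diary itself reveals the arm. Costs of Dental Treatment lists its contents: clinic visits, procedures, times, costs, escort and days off. None of these records allocation, so that route is not supported.

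The room for judgement is also limited. Caries is called only at cavitation, fillings and teeth missing through caries count too, and both arms receive home visits and leaflets. The under-calling rates above have no source in the document, and at 10% the change is only from 5% to about 7%. Finally, a condensed article may leave masking to a full protocol.

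What stands: three sections assign these tasks to one role with no separation, so the point does not rest on silence alone. Separate staffing is possible but not required. Even with it, the combined 24-month visit leaves the examiner open to disclosure by the parent. Cavitation-stage diagnosis and calibration reduce judgement and variability without hiding the arm.

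**Conclusion.** The point holds as a gap in role separation. Following the plan as written allows the primary outcome to be read with knowledge of the arm, through earlier visits, through the parent, or through another family from the same kindergarten. It does not show that examiners will be unmasked or that the result will be biased. The direction and size of any bias cannot be derived from the document.

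The figures of about 7%, 14% and 28% show sensitivity only. They depend on assumed under-calling of 10%, 20% and 30% confined to the intervention arm, 20% incidence, no true effect, and 147 children per arm treated as independent although kindergartens are allocated. This is an inexpensive improvement worth making and does not invalidate the design. Participants were still being recruited when the article was written, so on that timing the 24-month examinations could still be protected.

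**What to change.** Amend The 2-Year Follow-Up Data to state that:

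1. the 24-month examiner is not given the kindergarten allocation list;
2. the oral examination is done and recorded before the ECOHIS or any interview with the parent;
3. parents are asked beforehand not to mention the visits they received;
4. the examiner records whether the arm became known;
5. where the existing calibrated team allows, examiners are assigned to kindergartens whose families' homes they did not visit.

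Item 5 can only be conditional, because the article gives neither the number of calibrated examiners nor the number of kindergartens. If a full protocol already separates these roles, one sentence saying so is enough.

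The cost is a short amendment, some scheduling effort and less freedom in assigning researchers to homes. No extra assessor is required.

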### Data Analysis

Data collected from each visit will be checked for completeness by the research team members before it is keyed into SPSS. All the outcomes measures will be analyzed using the SPSS Program. Descriptive statistics will be used to report new caries teeth, OHRQoL, cost of DHVs and ELs, and the incremental cost effectiveness ratio (ICER) at 6, 12, and 18 months, as well as at the end of the 2-year follow-up period. A *t* test will be used for comparison of means of those parameters between the two groups and over the period of study. Logistic regression analysis will be carried out to test the influence of individual characteristics and on the CEA of the intervention in preventing caries.

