### Sample Size and Randomization

It is estimated that there will be a 5% of incidence of caries in the intervention group during the follow-up, compared with 20% in the control group. This is based on the findings of a study conducted in 2015 by Koh et al that reported a 4% of incidence of caries in the intervention group and 39% in the control group [11]. Using a statistical software, Epi info 7 (Center for Disease Control and Prevention, USA, 2015), a sample size calculation was conducted and a minimum sample of 176 subjects is needed to detect a 15% difference in incidence of caries, with a significance level of 95% and a power of 80% [16]. The researchers decided to aim for doubling the effective sample size to 300 subjects to ensure the effective sample size will be higher than 176 with a high power. After taking sampling error into account and the assumption of a 30% nonresponse rate, followed by the assumption of another 30% of drop-out rate, a total of 600 subjects will be approached to participate in this study.

The kindergartens that agreed to participate will be randomly allocated into either the intervention or control group (1:1) by a random “draw” method. No matching will be done since they all have a similar socioeconomic background. All children aged 5 or 6 years at the participating kindergartens, with parents’ consent to participate, will be included in the study [17].

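### Kindergartens are randomised, but the planned t tests and logistic regression treat children as independent, so p-values will be too small and intervals too narrow

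*Protocol article*

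**What the plan says.** Under Sample Size and Randomization the protocol states: "The kindergartens that agreed to participate will be randomly allocated into either the intervention or control group (1:1"), by drawing lots. There is no matching, for the reason that "No matching will be done since they all have a similar socioeconomic background". Enrolment within a kindergarten is complete: "All children aged 5 or 6 years at the participating kindergartens, with parents’ consent to participate, will be included in the study".

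Outcomes belong to the child. The primary outcome in Outcome Measures is new caries, "measured by the number of children included in the study with new caries, over a period of 2 years". New carious teeth, the ECOHIS score and the dental costs in the family's diary are also recorded child by child.

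Data Analysis names the methods. After listing new carious teeth, OHRQoL, the cost of visits and leaflets, and the ICER, it says a *t* "test will be used for comparison of means of those parameters between the two groups and over the period of study". It continues: "Logistic regression analysis will be carried out to test the influence of individual characteristics". No section mentions clustering, an ICC, a design effect, a mixed model, GEE, cluster-robust errors or kindergarten-level summaries.

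**The concern.** A standard *t* test or logistic regression on children takes each child as independently allocated. Here all children of a kindergarten are allocated together. They plausibly share a neighbourhood, diet habits and access to dental services, and so resemble one another in caries, ECOHIS and cost. The protocol does not discuss this; the correlation is a reasonable expectation, not a documented fact.

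If it is positive, the difference between arms carries between-kindergarten variation that the standard error leaves out. A difference that arises because the draw put kindergartens with more caries in one arm could then be reported as an effect of home visits. The same applies to the OHRQoL and cost comparisons, and so to the cost-effectiveness claim.

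This is not a detail that a condensed article leaves to an analysis plan. The article fixes both the randomised unit and the tests, and the two do not fit together.

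**Working it through.** **1. Does the plan treat children as independent? Reproduce the stated 176.** Sample Size and Randomization expects "5% of incidence of caries in the intervention group during the follow-up, compared with 20% in the control group", with 80% power; the significance level is taken as two-sided 0.05.

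- Mean proportion = (0.05 + 0.20)/2 = 0.125; difference d = 0.15.
- Per arm without continuity correction: n = [1.96 × √(2 × 0.125 × 0.875) + 0.842 × √(0.05 × 0.95 + 0.20 × 0.80)]² / 0.15² = (0.917 + 0.383)² / 0.0225 ≈ 75.1, so 76 per arm and 152 in total.
- With continuity correction: (75.1/4) × [1 + √(1 + 4/(75.1 × 0.15))]² ≈ 87.95, so 88 per arm and **176 in total**, the stated figure.

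The formula for individually randomised children therefore gives the protocol's number exactly. No design effect is included.

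**2. Number analysed.** 600 approached, 30% non-response, then 30% drop-out: 600 × 0.7 × 0.7 = 294. The number of kindergartens is not given. Assuming 20 kindergartens gives about 15 analysed children each; assuming 10 gives about 30 each.

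**3. Effect on the tests.** With m analysed children per kindergarten:

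- design effect DE = 1 + (m − 1) × ICC
- true two-sided error of a nominal 5% test = 2 × [1 − Φ(1.96/√DE)]
- factor by which intervals are too narrow = √DE

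Example, m = 15 and ICC 0.05: DE = 1 + 14 × 0.05 = 1.70; 1.96/√1.70 = 1.50; error = 0.133; factor 1.30.

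| m | ICC | DE | True error | Interval factor |
|---|---|---|---|---|
| 10 | 0.01 | 1.09 | 0.060 | 1.04 |
| 10 | 0.05 | 1.45 | 0.104 | 1.20 |
| 10 | 0.10 | 1.90 | 0.155 | 1.38 |
| 15 | 0.01 | 1.14 | 0.066 | 1.07 |
| 15 | 0.02 | 1.28 | 0.083 | 1.13 |
| 15 | 0.05 | 1.70 | 0.133 | 1.30 |
| 15 | 0.10 | 2.40 | 0.206 | 1.55 |
| 30 | 0.01 | 1.29 | 0.084 | 1.14 |
| 30 | 0.02 | 1.58 | 0.119 | 1.26 |
| 30 | 0.05 | 2.45 | 0.211 | 1.57 |
| 30 | 0.10 | 3.90 | 0.321 | 1.97 |

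**4. Check by simulation.** Binary caries outcomes were simulated from a beta-binomial model with no treatment effect, 3000 runs per setting, at ICC 0.02 / 0.05 / 0.10.

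- 10 kindergartens per arm, 15 children each: the child-level test rejected in 9.1% / 14.4% / 22.1% of runs.
- 5 per arm, 29 children each: 11.8% / 19.6% / 31.5%.
- A *t* test on kindergarten-level results stayed between 4.9% and 5.7%.

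**5. Does the larger target of 300 help?** It raises power but does not correct the standard error, so the p-values stay too small at any sample size. For a fixed number of kindergartens, more children in each makes DE larger.

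**The case against.** - **The unit of analysis is inferred.** Data Analysis does not say that the *t* test is run on children, and a *t* test on kindergarten means would fit the sentence. But the outcomes are per child, the regression concerns individual characteristics, no aggregation is described, and the sample size assumes independent children. The child-level reading is the natural one. If kindergarten means were intended, the text has to say so.
- **The size rests on assumptions.** Cluster size, number of kindergartens and ICC have no source in the protocol. Similar socioeconomic background, advice given family by family at home, and a final examination at age 7 or 8 could all lower the ICC. At ICC 0.01 with 10 children per kindergarten the error is only 6.0%, and errors of 21% to 32% describe the upper part of the range. This stands. It limits the size, not the direction: similar average background does not make the correlation zero.
- **No confidence intervals are announced.** True; the point about intervals applies to any that are derived from these tests or models.
- **The logistic regression may not be the treatment comparison.** Its stated purpose is unclear, so the *t* test is the main evidence. The regression has the same fault when fitted to children without a kindergarten term.
- **The simulation covers only a binary outcome.** The design-effect formula carries over to teeth, scores and costs, but each may have its own ICC.

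**Conclusion.** The concern holds and must be fixed before analysis. The stated tests do not match the stated randomisation, and nothing elsewhere in the protocol repairs this. For any positive correlation within kindergartens, the comparisons of caries, ECOHIS and cost have a type I error above 5%. Over assumed cluster sizes of 10 to 30 and ICCs of 0.01 to 0.10 it lies between 6.0% and 32.1%, with intervals too narrow by a factor of 1.04 to 1.97. The design effect alone does not show the further loss with few kindergartens, where degrees of freedom should follow the number of kindergartens and not the number of children.

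**What to change.** Rewrite Data Analysis so that it follows the randomised unit:

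- **Mixed models** with a random intercept for kindergarten: linear for ECOHIS and cost with Satterthwaite or Kenward-Roger degrees of freedom, logistic for new caries.
- **With few kindergartens per arm**, a *t* test on kindergarten-level summaries with degrees of freedom equal to kindergartens minus 2.
- **Fix the choice in advance.** State the number of kindergartens at which the second option applies, or make the kindergarten-level test primary from the start. For caries this matters most: about 147 children per arm at 5% gives 0.05 × 147 ≈ 7 events in the intervention arm, so a random-intercept logistic model may be unstable. Kenward-Roger is a linear-model correction and does not carry over directly to it.
- **Report** the number of kindergartens per arm and the ICC for each outcome.

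The wording changes and each child's kindergarten must be in the data set. SPSS has mixed-model procedures, so the software can stay. The statistical price is wider intervals and lower power: with 300 children, power for 5% against 20% is 0.978 if children were independent, 0.809 at 20 per kindergarten and ICC 0.05, and 0.512 at 30 and ICC 0.10. Recruitment is still under way, so the sample size can be revisited with a design effect. At 20 per kindergarten and ICC 0.05, for example, the minimum of 176 becomes 176 × 1.95 = 343.2, or 344.
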